## Abstract

**Background:**

Fifty thousand knee replacements are performed annually in the UK at an estimated cost of £150 million. Post-operative improvement depends on a number of factors including implant design and patient associated factors. To our knowledge there are no published study's comparing the results of AP glide and rotating platform designs of LCS knee arthroplasty. Therefore we feel that a study is required to investigate and compare the effects of two types of LCS total knee arthroplasty on joint proprioception and range of motion.

**Methods/Design:**

Patients will be randomised to receive either a LCS AP glide or Rotating platform prosthesis. Clinical scores (Oxford knee score, American knee society score, EuroQol), range of motion and proprioception will be assessed prior to and at 3,6, 12 and 24 months after the operation. Proprioception will be assessed in terms of absolute error angle (mean difference between the target angle and the response angle). Knee angles will be measured in degrees using an electromagnetic tracking device, Polhemus 3Space Fastrak that detects positions of sensors placed on the test limb. Student's t-test will be used to compare the mean of two groups.

**Discussion:**

Evidence is lacking concerning the best prosthesis to use for patients undergoing total knee replacement. This pragmatic randomised trial will test the null hypothesis that anteroposterior glide LCS knee arthroplasty does not result in better post operative knee motion and proprioception as compared to rotating platform LCS knee.

**Trial Registration:**

ISRCTN52943804

## Background

Total knee replacement surgery is one of the commoner types of replacement surgeries performed nowadays with about 50,000 knee replacements being performed annually in the UK. Fixed bearing total knee arthroplasty (TKA) has been used as a standard treatment for osteoarthritis of the knee joint. It allows fairly unconstrained motion of the knee joint. Flexion and extension of the knee involve antero-posterior gliding, rotation and femoral rollback, which are not reproduced in fixed bearing TKA.

The LCS (low contact stress) rotating platform TKA system attempts as near-normal reproduction of knee motion as possible, minimising interface stresses by allowing rotation (with this design, the posterior cruciate ligament has to be sacrificed). The AP (antero-posterior) glide LCS type allows both antero-posterior glide and rotation. With this design, the posterior cruciate ligament needs to be intact to allow normal femoral rollback. Rather than imposing a predetermined pattern of motion, the AP glide design permits bearing movement, which corresponds to the requirements of individual patient anatomy. We hypothesise that these features of the AP glide TKA may allow improved joint position sense (proprioception) and better overall functional outcome.

The LCS rotating platform design has good clinical results, but, as results improve in terms of flexion and long term survival, more subtle measures of the return to near normal post-operative function become important. Proprioception is affected by osteoarthritis of the knee joint [1]. As proprioception is one of the protective mechanisms of a joint, one should aim to preserve or enhance it. Proprioceptive function after TKA is debated, with studies reporting conflicting results [2-4]. Post-operative improvement depends on a number of factors, including implant design and patient-associated factors. To our knowledge, there are no published studies comparing the results of AP glide and rotating platform TKA.

## Methods/Design

### Null Hypothesis

Antero-posterior glide LCS knee arthroplasty does not result in better post-operative knee motion and proprioception as compared to rotating platform LCS knee arthroplasty.

### Objectives

The trial proposes to:

1. Study the improvement in knee motion and overall function after AP glide and rotating platform design LCS TKA.

2. Examine the effect of this intervention on proprioception.

### Trial Summary

This study aims to compare the post operative knee motion and proprioception after LCS AP glide and rotating platform knee replacement designs. We propose to recruit a total of 50 patients (25 in each group) in the trial. The patients will be recruited from the pre-operative assessment clinic following their informed consent to take part in the study. Randomisation will take place at the time of surgery. The primary outcome measure will be the knee motion and prorioception. The secondary outcomes will include the Oxford Knee Score [5], American Knee Society Score [6], EuroQol EQ-5D [7], and post-operative complications. All outcomes will be evaluated at 3, 6, 12 and 24 months after the index surgery.

### Study type

A randomised controlled trial comparing the effects of AP glide and rotating platform design LCS TKA.

#### Participants

Participants will be patients undergoing primary bi- (tibio-femoral joint) or tri- (tibio-femoral-patellar joint) compartmental knee arthroplasty. Patients will be recruited from the Orthopaedic Pre-operative clinics held at the Orthopaedic Outpatient Department of the City General Hospital, Stoke on Trent, England.

#### Treatment details

All surgical procedures will be performed in the operating theatres of the City General Hospital, Stoke on Trent, England. In the operating theatre, patients will be randomised to receive one of the two types of prosthesis using a standard surgical technique.

#### Eligibility

Patient will be included if:

1. They require a primary bi- or tri-compartmental knee replacement.

2. They have given their voluntary, written informed consent.

Patients will be excluded if:

1. They are going to have revision knee surgery.

2. They are scheduled to have bilateral knee replacement in one sitting.

3. They suffer from rheumatoid arthritis, diabetes mellitus, posttraumatic arthritis or any form of neurological disorder, which can affect the joint position sense.

4. They have had or will require a major knee arthrotomy on the other same side within 6 months period.

5. They have more than 20° of varus, valgus or flexion deformity

#### Recruitment

Patients will be recruited from the orthopaedic pre-operative assessment clinic. Their medical notes will be screened to assess suitability. At the pre-operative visit, patients will be informed of the nature of the study by their consultant orthopaedic surgeon. Eligible patients will be provided with an information leaflet explaining the nature of the study. They would be invited to ask questions regarding the study. They will then be given the opportunity to think about whether they would like to participate or not. During this period, they will be contacted by the research nurse to discuss their participation and to answer any questions they may have. On the day of the admission, the patients will have a further opportunity to discuss the participation in the trial. Patients willing to take part in this trial will be then invited to sign a consent form by a member of the research team with the approval of the operating consultant. Baseline data will be acquired on admission. Once patients have consented for the study, they will then be randomised in the operating theatre.

#### Randomisation

Patients will be randomised using a minimisation programme called Minim [8]. On arrival in the operating suite, eligibility criteria for each patient will be re-checked. Randomisation will take place once the knee replacement surgery is started and it is decided that either of these two TKA designs could be used. The patient will be allotted a group, i.e. AP glide knee replacement or rotating platform knee replacement. Provision will be made for an easy access to the randomisation service on the operating theatre computer. The patients in both groups will have post-operative rehabilitation regime as prescribed by the operating surgeon. Any complication during or after the operation will be noted. Patients will then be seen at their post operative visit at 3, 6, 12 and 24 months where knee score forms will be completed, proprioception will be evaluated and range of joint movement will be quantified using the FASTRACK system (*Polhemus Fastrack 3Space Manual*, Polhemus Inc, Colchester, VT, 1992).

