### Statistical considerations

#### Sample size

The sample size of the trial has been calculated on the basis of a pilot study. Range of motion of the knee joint is the primary outcome in our study. We found that the standard deviation for this parameter in the pilot study was 20°. The anticipated difference between the mean (which we think would be of clinical significance) was considered as 20°. The sample size required for an alpha of 0.05 and a power of 90% was found to be 22 cases per group. To allow for dropouts, recruitment a total of 25 patients in each group of the study would be a reasonable option.

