#### Analysis

*t *test will be used to compare variables between the groups where the data are approximately normally distributed, possibly after transformation. Non-normal data will be assessed using the Mann-Whitney test. Any imbalances between the groups at baseline will be adjusted for by using ANCOVA. Analysis will be performed using the intention to treat criterion.

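### Allocation is by minimisation but adjustment depends on observed baseline imbalance, so the minimised factors would usually be left out; if they are prognostic, the unadjusted test is conservative

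*Protocol article*

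**What the plan says.** Protocol article, Randomisation: "Patients will be randomised using a minimisation programme called Minim". The article does not name the factors, their weights or any random element.

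Protocol article, Abstract (Methods/Design): "Student's t-test will be used to compare the mean of two groups". The Analysis section says the same with a condition: the t "test will be used to compare variables between the groups where the data are approximately normally distributed", with Mann-Whitney otherwise.

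The same section then gives its only route to covariate adjustment: "Any imbalances between the groups at baseline will be adjusted for by using ANCOVA". That sentence does not mention the minimisation factors.

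Protocol article, Sample size: "Range of motion of the knee joint is the primary outcome in our study". The calculation uses an SD of 20° with no reduction for covariates, a difference of 20°, alpha 0.05 and 90% power, and gives 22 per group. The recruitment target is 25 per group.

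**The concern.** The allocation method and the adjustment rule work against each other. Minimisation makes the arms alike on chosen factors. The analysis adjusts only for variables on which the arms turn out to differ. The factors singled out for control are therefore the ones that the rule would usually omit.

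When a balanced factor predicts the outcome, the treatment difference varies less from trial to trial than under simple randomisation. The t-test does not see this. Its standard error still contains the variance between factor levels, so it overstates the uncertainty. Type I error then falls below 5%, the interval is wider than it needs to be, and the precision bought by minimising is not reported. The rule also lets the data choose the covariates.

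**Working it through.** **Inputs.** From the Sample size section: "We found that the standard deviation for this parameter in the pilot study was 20" degrees; "The anticipated difference between the mean (which we think would be of clinical significance) was considered as 20" degrees; alpha 0.05; power 90%; 22 per group, hence 44 analysed. Assumed, because the article does not give them: three binary minimisation factors with equal effects, and R², the share of outcome variance that they explain, at 0, 0.1 and 0.3.

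**1. The plan's own figure.** n per group = 2 × (1.960 + 1.282)² × (20/20)² = 21.0, which rounds up to 22. This is two-sided; a one-sided alpha would give 18. Exact noncentral-t power at 22 per group is 89.97%. The stated size reproduces, and it matches an unadjusted t-test.

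**2. Standard errors by formula.** The t-test reports about SD × √(2/n) = 20 × √(2/22) = 6.03°. With the factors balanced, the true standard error is about 20 × √(1 − R²) × √(2/22):
- R² = 0: 6.03°, ratio 1.00
- R² = 0.1: 18.97 × 0.3015 = 5.72°, ratio 1/√0.9 = 1.054
- R² = 0.3: 16.73 × 0.3015 = 5.04°, ratio 1/√0.7 = 1.195

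The approximate type I error of the unadjusted test is 2 × [1 − Φ(1.96 × ratio)]. At R² = 0.1 this is 2 × [1 − Φ(2.066)] = 3.9%. At R² = 0.3 it is 2 × [1 − Φ(2.343)] = 1.9%.

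**3. Simulation.** 44 patients, deterministic minimisation on the three factors, SD 20°, 4,000 runs per setting. Each cell gives t-test / ANCOVA on the factors.

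| Assumed R² | Type I error | Mean SE under the null | Power at 20° |
|---|---|---|---|
| 0 | 5.1% / 5.1% | 5.98° / 5.99° | 90.1% / 90.0% |
| 0.1 | 3.5% / 4.5% | 6.00° / 5.69° | 91.6% / 93.4% |
| 0.3 | 1.9% / 4.9% | 6.01° / 5.03° | 93.0% / 97.2% |

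The empirical SD of the unadjusted estimate under the null was 6.06°, 5.66° and 5.06°. At R² = 0.3 the t-test therefore reports about 6.0° for an estimate that really varies by about 5.1°. Monte Carlo error is √(0.05 × 0.95/4000) = 0.3 points on a 5% rate and √(0.9 × 0.1/4000) = 0.5 points on a 90% rate.

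Other runs, some with allocation to the preferred arm at probability 0.8, widen the t-test's type I error to 3.2–3.8% at R² = 0.1 and 1.9–2.6% at R² = 0.3. Adjusted power at R² = 0 was 89–90%.

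**4. Interval width.** The 95% half-width is t × mean SE, with 42 degrees of freedom unadjusted (t = 2.018) and 39 adjusted (t = 2.023):
- R² = 0.1: 2.018 × 6.00 = 12.1° against 2.023 × 5.69 = 11.5°
- R² = 0.3: 2.018 × 6.01 = 12.1° against 2.023 × 5.03 = 10.2°

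**5. Planned power.** Unadjusted power at 20° rises slightly with R² because minimisation reduces the true variance while the reported standard error stays near 6.0°. It does not fall below the planned level beyond simulation error. The forgone gain is 93.4 − 91.6 = 1.8 points at R² = 0.1 and 97.2 − 93.0 = 4.2 points at R² = 0.3.

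**The case against.** The strongest reply is that the loss is conditional and errs on the safe side. The article gives neither the factors nor their prognostic strength. At R² = 0 the two analyses are equivalent. There is no bias and no excess of false positives. The trial was sized on an SD without covariate reduction, so the t-test delivers what was planned. All of this stands, and it limits the point to precision and calibration.

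It can also be said that a journal article leaves the factor list and model covariates to fuller documents. That stands for the factor list, whose absence is not criticised here. It does not cover the ANCOVA sentence, which is a stated rule that a later analysis plan would inherit.

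Three stronger readings are tempting, and the documents do not support them.
- A reader might infer that the trial is underpowered. At the planned 20° it is not. A larger gap appears at 15° (69.8% against 82.2% at R² = 0.3), but the documents nowhere plan for a 15° difference.
- A reader might infer that standard errors are certainly too large. That requires prognostic factors, which are plausible but not documented.
- A reader might infer that the factors could never be adjusted for. Minimisation in 50 patients, particularly with a random element, reduces imbalance without excluding it, so the accurate word is "usually".

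Mann-Whitney takes no covariates either, but it was not simulated, and the figures above do not apply to it.

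**Conclusion.** The point holds in a conditional form. The stated adjustment rule does not fit the stated allocation method. To the extent that the minimised factors predict range of motion, the default test is conservative and its interval too wide. For factors explaining 10% to 30% of variance, the half-width is about 0.6° to 1.9° wider than it need be (12.1 − 11.5 and 12.1 − 10.2).

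These sizes rest on the assumed R², three equally weighted binary factors and 44 analysed patients. This is a worthwhile, low-cost improvement, and it does not undermine the trial's validity or its sample size.

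**What to change.** In the Analysis section, replace the imbalance-triggered ANCOVA with a statement such as: the primary outcome will be compared by ANCOVA including all minimisation factors and pre-operative range of motion, whatever their observed balance; the unadjusted test is a sensitivity analysis. Bring the Abstract's method sentence into line.

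The sample size can stay, since an SD without covariate reduction is cautious for an adjusted analysis. The figures above cover the minimisation factors only; any gain from pre-operative range of motion would be additional and is not quantified here.

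No new data are needed: the factors must be known to run the allocation, and range of motion is already measured before operation. The cost is one sentence and one degree of freedom per covariate term, with at most about a 1-point loss of power if the factors turn out not to be prognostic.

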### Assesment of outcome

All the assessment procedure will be performed in the Bionics Laboratory, City General Hospital, Stoke on Trent, England.

#### Secondary outcomes

1. Proprioception, as measured by absolute error angle, i.e. the difference between actual and perceived angle through which the joint has been moved passively, will be measured using the Fastrak apparatus (Polhemus, Colchester, VT, USA). Briefly, each subject will have their knee screened from view while sitting on an examination couch with the knees hanging from the side. Each knee will be moved passively to one of three predetermined position (full extension, 30° and 60° of flexion), and held in that position for 5 seconds. The limb will then returned to a resting position. The patient is then asked to reproduce the knee position to which it had been moved passively. The test will be repeated three times per each of three positions.

2. The American Knee Society Score [6], Oxford Knee Score [5], and EuroQol EQ-5D [7] will be recorded pre-operatively and at 3,6,12 and 24 months after the operation.

3. Complications.

### Statistical considerations

#### Sample size

The sample size of the trial has been calculated on the basis of a pilot study. Range of motion of the knee joint is the primary outcome in our study. We found that the standard deviation for this parameter in the pilot study was 20°. The anticipated difference between the mean (which we think would be of clinical significance) was considered as 20°. The sample size required for an alpha of 0.05 and a power of 90% was found to be 22 cases per group. To allow for dropouts, recruitment a total of 25 patients in each group of the study would be a reasonable option.

#### Analysis

*t *test will be used to compare variables between the groups where the data are approximately normally distributed, possibly after transformation. Non-normal data will be assessed using the Mann-Whitney test. Any imbalances between the groups at baseline will be adjusted for by using ANCOVA. Analysis will be performed using the intention to treat criterion.

#### Blinding

The laboratory personnel will be blinded to the treatment allocation, and will perform knee motion and proprioceptive assessments. The research nurse, who will be blinded to the treatment allocation, will perform the knee scoring of both groups.

#### Data collection

The data will be collected from the medical records during the in hospital stay of the patients. Final data collection will take place at the post-operative visit at 24 months. The last observation will be carried forward for data analysis.

#### Protocol deviations

Any changes to the protocol will be recorded. Any amendments that may be required once the trial has started will be submitted for approval by the ethics committee.

#### Informed consent

All eligible patients who agree to take part will sign an informed consent form. They will confirm that they have been given the information that they require, and that the study has been explained to them.

#### Confidentiality

Only the trial organisers/administrators will have access to patients' notes and questionnaires. All recorded information will be stored separately from patients' names and addresses.

#### Ethics

The trial has been given ethics permission by our Local Ethics Committee, and is registered as ISRCTN 52943804.

## Discussion

Evidence is lacking concerning the best prosthesis to use for patients undergoing total knee replacement. This pragmatic randomised trial will test the null hypothesis that anteroposterior glide LCS knee arthroplasty does not result in better post-operative knee motion and proprioception as compared to rotating platform LCS knee.
